#### Secondary outcome measures (compare between arms)

Operation time: The time from the start of the operation to the end of the operation.

Length of stay: The time from admission to discharge.

Estimated blood loss. Blood loss will be defined as the total volume of suctioned fluids minus the volumes of irrigation fluids used at the completion of surgery.

The levels of CD4^+^ T lymphocytes, NK cells, and CD4^+^ CD25^high^ CD127^low^ Treg in peripheral blood before and after operation; postoperative peritoneal immune factors IL-6, TNF-β, and TNF-α levels.

Hemodynamic parameters (cardiac output before and at the end of surgery, CO), mean arterial pressure (MAP), and stroke output (stroke volume (SV)). Pco2, blood gas analysis, ion profile.

Intraoperative complications (injury to bladder, ureters, bowel, blood vessels and bleeding, and nerves).

Perioperative complications: urinary tract infection, urinary retention, ileus, myocardial infarction, atrial fibrillation, pulmonary edema, atelectasis, pneumonia, renal and cerebrovascular morbidity, and thromboembolic complications (deep vein thrombosis, pulmonary embolism).

Early (4 weeks) postoperative complications: pulmonary, renal, and cerebrovascular morbidity; wound and vault complications (infection, breakdown, and dehiscence); septicemia and thromboembolic complications (deep vein thrombosis, pulmonary embolism); and lymphocyst or abscess formation.

Delayed postoperative complications (4 weeks–6 months after surgery): lymphedema, incisional hernia formation, vaginal evisceration.

Postoperative pain and analgesic consumption using pain scores and analgesic consumption measurements.

Costs: measured as the incremental cost/unit of improvement in functional outcome, measured in terms of the primary outcome plus using quality-adjusted life years to undertake a cost-use analysis.

The quality of life instruments(QOL) (FACT-Cx, SF12, EQ-5D, MDASI): change in QOL using functional assessment of cancer therapy-cervical between baseline (presurgery) and 6 months after surgery.

Pelvic floor distress inventory: measures symptom severity and QOL changes in women with pelvic floor disorders. The pelvic floor distress inventory provides a standardized, reproducible assessment of the patient’s symptoms and their effect on daily life.

The OS at 4.5 years follow-up [8].

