### Sample size

The main purpose of this study is to determine whether gasless laparoscopic radical hysterectomy (gasless TLRH) or equivalent to total abdominal hysterectomy (TARH) is effective in terms of disease-free survival at 4.5 years. If the difference in disease-free survival rate does not exceed 7%, then these two surgeries are considered equivalent.

The estimated 4.5-year disease-free survival rate of patients receiving TARH is 90%. The sample size was based on an expected disease-free survival rate of 90% in the open-surgery group at 4.5 years and a noninferiority margin of 7.2 percentage points for minimally invasive surgery, which reflected an acceptable difference in the expected survival rate of at most 8 percentage points. In previous studies involving patients with other types of cancer, a noninferiority margin of 6 to 8 percentage points has been considered to be clinically acceptable.

Based on these data, a total of 740 patients (370 in each group) will be sufficient to declare equivalence in 4.5 years of accrual and 4.5 years of follow-up, with an equivalence margin of 6% or less at 4.5 years [8].

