#### Phase II analysis (phase III study)

The disease-free survival and overall survival curves will be estimated using the Kaplan–Meier method. The main comparison of survival distribution will be compared with the logrank test. The secondary analysis will use appropriate regression models (such as Cox proportional risk models) to adjust for prognostic factors. All efficacy indicators will be compared through intention-to-treat analysis, including all randomized patients. The toxicity will be analyzed based on the treatment received. The difference between treatment groups will be reported with a 95% confidence interval.

Descriptive statistics on treatment-related adverse events and quality of life (FACT-Cx, SF-12). At each evaluation, subscales (Physical Health, Social Health, Emotional Health, Functional Health, Cervical Cancer Specific Health, and Body Image Scale) will be calculated for each random group.

Similarly, descriptive statistics will be calculated for other results, such as pain score, anxiety and depression score, Analgesic consumption, etc.

The normality of continuous variables and the equality of inter-group variance will be evaluated.

Discrete variables (such as the presence/absence of postoperative infection) will be summarized as follows frequency/proportion.

For continuous variables, analysis of variance and/or regression analysis will be used where appropriate. If the assumptions of these tests are violated, alternative non-parametric tests will be used. Differences between groups with respect to discrete variables will be assessed using the chi-squared test.

Exploratory analysis adjusts prognostic factors including age, tumor size, staging, and tumor grading.

Differentiation, depth of muscle invasion, lymph node involvement, treatment type, and ECOG status will be evaluated using proportional risk regression methods. The impact of baseline quality of life on survival will also be studied.

We will analyze the results related to treatment costs based on different surgical methods [8].

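### Continuous secondary outcomes: no adjustment for the outcome's own baseline is specified, and the quantity compared can change with a check of the data

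*Protocol article*

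**What the plan says.** Under Secondary outcome measures, a list headed as comparisons between arms, the quality-of-life entry is the "change in QOL using functional assessment of cancer therapy-cervical between baseline (presurgery) and 6 months after surgery".

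Under Phase II analysis (phase III study), the rule for continuous variables has three parts:

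- The check on the data: "The normality of continuous variables and the equality of inter-group variance will be evaluated"
- The default method: "For continuous variables, analysis of variance and/or regression analysis will be used where appropriate"
- What happens when the check fails: "If the assumptions of these tests are violated, alternative non-parametric tests will be used"

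The same section promises a 95% confidence interval for differences between treatment groups, and descriptive statistics for quality of life by arm at each evaluation. It mentions adjustment in these words: "Exploratory analysis adjusts prognostic factors including age, tumor size, staging, and tumor grading". The text that follows lists further clinical factors and names proportional hazards regression. The baseline value of a continuous outcome is not among the factors listed. Baseline quality of life appears once more: "The impact of baseline quality of life on survival will also be studied".

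Table 1 ticks FACT-Cx, SF-12, EQ-5D, MDASI and immune factors at baseline, 1 week, 6 weeks, 3 months and 6 months. It ticks the pelvic floor inventory (PFD) at baseline and 6 months.

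**The concern.** Two features of the rule make the secondary comparisons weaker than the data allow.

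First, a raw change score gives the baseline a fixed weight of one. When the baseline-to-follow-up correlation is moderate, that over-corrects and adds noise. Regressing the follow-up value on its baseline lets the data set the weight, and in a randomized trial it is at least as precise in large samples.

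Second, whether arms are compared on means or on ranks is settled after looking at the distributions. The article names no check, threshold, replacement test or effect estimate. Two outcomes, or one outcome at two visits, could then be reported on different scales. A rank test does not by itself give the difference with a confidence interval that the same section promises.

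At stake is the precision and consistency of the quality-of-life, pelvic floor and immune comparisons. The Discussion's expectation of better short-term well-being after the laparoscopic procedure leans on outcomes of this kind.

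**Working it through.** The article gives no SD, effect size or power for any continuous outcome, so there is no stated figure to reproduce.

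**Inputs**
- Patients per arm: 370, from Sample size ("a total of 740 patients (370 in each group) will be sufficient to declare equivalence"). All are assumed to contribute at 6 months.
- SD at baseline and 6 months: not given; assumed equal.
- Baseline-to-6-month correlation r: not given; range 0.3 to 0.8 assumed.
- Illustrative true difference: 0.2 SD, two-sided alpha 0.05 (assumed).

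**Precision.** Variance factors relative to SD²:
- follow-up value only: 1
- unadjusted change score: 2(1 − r)
- baseline-adjusted (ANCOVA): 1 − r²

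ANCOVA over change = (1 − r²) / [2(1 − r)] = (1 + r)/2, so change over ANCOVA = 2/(1 + r). The standard error of the difference is SD × √(2 × factor / 370). The effective number per arm is 370 × (1 + r)/2.

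| r | Change factor | ANCOVA factor | Change / ANCOVA variance | 370 per arm on change is worth, under ANCOVA | Power at 0.2 SD: change | Power at 0.2 SD: ANCOVA |
|---|---|---|---|---|---|---|
| 0.3 | 1.40 | 0.91 | 1.54 | 241 | 63.3% | 81.4% |
| 0.5 | 1.00 | 0.75 | 1.33 | 278 | 77.6% | 88.1% |
| 0.7 | 0.60 | 0.51 | 1.18 | 315 | 94.0% | 96.8% |
| 0.8 | 0.40 | 0.36 | 1.11 | 333 | 99.0% | 99.5% |

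Worked line at r = 0.3: the SE on change is √(2 × 1.40/370) = 0.0870 SD and under ANCOVA √(2 × 0.91/370) = 0.0701 SD. The ratio 0.0701/0.0870 = 0.81, so the adjusted interval is about 19% narrower. At r = 0.8, √0.90 = 0.95, about 5% narrower. Follow-up alone has power 77.6% at every r, so below r = 0.5 the change score is less precise than ignoring baseline altogether.

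**Switching rule.** The article names no formal check, so one was assumed: Shapiro-Wilk in each arm and Levene between arms, each at 0.05. Any rejection leads to Mann-Whitney, otherwise to the t-test. With 370 per arm, no true difference and 4,000 simulated trials:

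| Data | Switched to rank test | Type I error of the rule |
|---|---|---|
| Normal | 14% | 0.053 |
| Mildly skewed (gamma, shape 16) | 99.7% | 0.050 |

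The 14% is what three checks at 0.05 should give: 1 − 0.95³ = 0.143. The simulation error on a 5% rate is √(0.05 × 0.95/4000) = 0.003, so both error rates are compatible with 5%. The rule therefore changes what is compared, not how often it rejects falsely.

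**The case against.** A reader might infer that the plan throws the baseline values away. It does not: a change score uses baseline by subtraction, and baseline quality of life is also to be studied against survival. A reader might also infer that ANOVA is the only method. The wording allows regression, and ANCOVA and mixed models are regression, so the better analysis is already permitted. Both points stand. What is missing is a commitment to it, and permission for several methods where appropriate does not fix one.

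A covariate list for secondary models is ordinary SAP content, and the SAP is not shown. That is fair, and the absence of a named covariate would not carry the point alone. But the article does fix a change-from-baseline outcome and a conditional move to non-parametric tests. Both are stated choices with a better alternative at no cost in data.

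A third tempting inference is that test switching inflates false positives. The simulation does not support it. The article also names no formal test or alpha: the evaluation may be graphical, and the switching frequencies hold only under the assumed checks. A rank comparison can also carry an interval, such as Hodges-Lehmann, though that estimates a different quantity and the article does not name it.

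Finally, an unadjusted change-score comparison is unbiased under randomization, so this is a matter of efficiency. At high correlation the gain is small.

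**Conclusion.** The point holds as a low-cost improvement to secondary analyses, not as an error that threatens the trial. If change is compared unadjusted, the variance is 1.54 times (r = 0.3) down to 1.11 times (r = 0.8) the baseline-adjusted variance. This rests on equal SDs and on correlations that the article does not give. The data-dependent switch leaves the mean difference unprotected as the reported estimate, with no visible cost in type I error.

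The scope is limited. Operation time, blood loss and length of stay have no baseline value, and Table 1 shows no baseline pain score, so the precision argument does not reach them. The peritoneal cytokines are listed as postoperative measures, so among the immune outcomes it applies most clearly to the peripheral blood counts taken before and after operation. Only the quality-of-life entry, through FACT-Cx, is defined as a change to 6 months. The primary disease-free survival analysis is unaffected.

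**What to change.** State in the SAP that each continuous secondary outcome with a baseline is compared between arms by ANCOVA of the 6-month value adjusted for its baseline. Where there are several post-operative visits, the alternative is a mixed model over 1 week, 6 weeks, 3 months and 6 months with baseline and visit-by-arm terms. The pelvic floor inventory has no visit between baseline and 6 months in Table 1, so ANCOVA is the natural choice there. Report the adjusted mean difference with its 95% CI. The FACT-Cx definition can remain: with baseline in the model, analysing the change or the 6-month value gives the same estimated difference between arms.

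Keep the mean difference as the estimate whatever the normality check shows. For skewed outcomes, including length of stay and blood loss, use robust or bootstrap standard errors, and give a named rank test as a sensitivity analysis only.

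The cost is a few sentences of SAP wording, with no new data, visits or patients. It should be fixed before outcome data are compared by arm.

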### Abdominal radical hysterectomy

Antibiotics were given 30 min before surgery; a sequential compression device (SCD) was used. Make a median incision in the abdomen, all peritoneal surfaces should be thoroughly examined, the location of any metastatic disease should be recorded in the surgical report, and a biopsy should be performed to confirm the diagnosis. The posterior pelvic peritoneum was opened, suspected enlarged lymph nodes were removed, and frozen sections were submitted for examination. If the lymph nodes are positive, the aortic lymph nodes are sampled, but radical hysterectomy will be abandoned and the patient will receive definitive chemoradiotherapy. If the pelvic lymph nodes are not suspected, radical hysterectomy (Piver type 2 or 3) and pelvic lymph node dissection are possible, and the ovaries may be removed or preserved and/or transposed. Staging of aortic lymph node dissection includes removal of lymphoid tissue to submesenteric artery tissue. The days of catheter indwelling were recorded after operation.

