### Statistical analysis

The main endpoint will be analyzed based on the intention-to-treat principle.

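### The exploratory Cox analysis lists depth of invasion and nodal involvement, found at the randomised operation, and an undefined treatment type among its adjustment factors

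*Protocol article*

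**What the plan says.** All the analysis text is in the protocol article, sections Statistical analysis and Phase II analysis (phase III study).

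- **Primary.** "The main endpoint will be analyzed based on the intention-to-treat principle", and "The main comparison of survival distribution will be compared with the logrank test".
- **Secondary.** "The secondary analysis will use appropriate regression models (such as Cox proportional risk models) to adjust for prognostic factors". No factor is named there.
- **Exploratory.** "Exploratory analysis adjusts prognostic factors including age, tumor size, staging, and tumor grading". A new paragraph then continues the list: "Differentiation, depth of muscle invasion, lymph node involvement, treatment type, and ECOG status will be evaluated using proportional risk regression methods".
- **Analysis set.** "All efficacy indicators will be compared through intention-to-treat analysis, including all randomized patients".

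The two surgical sections (Abdominal radical hysterectomy, and the laparoscopic surgery in the open state) use the same text on nodes: "suspected enlarged lymph nodes were removed, and frozen sections were submitted for examination". If the nodes are positive, "radical hysterectomy will be abandoned and the patient will receive definitive chemoradiotherapy".

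**The concern.** An adjusted arm effect keeps the protection of randomisation when the covariates are fixed before allocation. Two of the listed factors, depth of invasion and nodal involvement, are recorded at or after the operation that was randomised. A third, treatment type, has no stated meaning.

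Two things can go wrong. Patients with no hysterectomy specimen have no specimen depth, and a standard Cox fit silently drops them. They are node-positive patients, so the omission is selective. In addition, surgeon and patient know the arm. If nodes or depth are ascertained differently by access route, conditioning on the recorded value makes the arms unlike each other.

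At stake is the adjusted hazard ratio. In an equivalence or non-inferiority trial it is likely to be read as support for the main result.

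**Working it through.** The plan states no figure on this point, so this is mainly a check of the text. Two illustrations on assumed inputs follow.

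**1. When each listed factor is known**

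| Factor | Where the protocol places it | Before randomisation? |
|---|---|---|
| Age, ECOG | Eligibility; ECOG also at baseline in Table 1 | Yes |
| Clinical stage | Table 1, baseline | Yes |
| Tumour size | CT and MRI at baseline (Table 1) | Yes, if the imaging value is meant |
| Grade, differentiation | Baseline assessments: baseline tissue confirms cell type and grade | Yes, if the biopsy value is meant |
| Lymph node involvement | Frozen section at operation; sentinel node biopsy in the surgery column of Table 1 | No |
| Depth of invasion | Stromal invasion in Table 2, in a section on findings at surgery | Not from the specimen |
| Treatment type | Not defined | Depends on the meaning |

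Treatment type could mean the randomised arm, the Piver type, the treatment received or adjuvant therapy. Only the first is fixed by randomisation.

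**2. Who lacks a depth value**

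The abandonment rule applies in both arms. Nodal status is known for these patients, because positive nodes trigger the rule. Specimen depth is what is missing. With N = 740 (Sample size) and an assumed abandonment rate f, the number missing is 740 × f:

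| f (assumed) | Missing depth | Left in a complete-case fit |
|---|---|---|
| 2% | 14.8, about 15 | 725 |
| 5% | 37 | 703 |
| 10% | 74 | 666 |
| 15% | 111 | 629 |

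**3. Does adjustment bias the arm effect?**

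A Cox simulation used a true arm hazard ratio of 1 and six runs of 40,000 patients per setting. Assumed inputs: 10% node-positive, hazard ratio 4 for positive nodes, and 92% disease-free at 4.5 years if node-negative. The overall event risk is then 0.90 × 0.08 + 0.10 × (1 − 0.92⁴) = 0.072 + 0.028 = 0.100, in line with the planned 90% disease-free survival. Ratios compare the two estimates from the same runs.

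| Nodes detected, open / laparoscopic | Method | Unadjusted HR | Resulting HR | Ratio |
|---|---|---|---|---|
| 100% / 100% | adjust for detected nodes | 0.968 | 0.969 | 1.00 |
| 100% / 100% | exclude detected node-positive | 0.944 | 0.936 | 0.99 |
| 100% / 70% | adjust | 1.005 | 1.074 | 1.07 |
| 100% / 70% | exclude | 0.983 | 1.078 | 1.10 |
| 70% / 100% | adjust | 1.002 | 0.940 | 0.94 |
| 70% / 100% | exclude | 1.024 | 0.934 | 0.91 |

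The unadjusted column should be 1 throughout, so its spread is simulation noise and the ratio is the figure to read.

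Hand check of exclusion at 100% / 70%. The open arm keeps only node-negative patients. The laparoscopic arm keeps 0.90 node-negative and 0.10 × 0.30 = 0.03 undetected node-positive. The initial hazard ratio is (0.90 + 0.03 × 4) / 0.93 = 1.02 / 0.93 = 1.10. With detection reversed it is 0.93 / 1.02 = 0.91. Both agree with the table.

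So equal detection leaves the arm effect essentially unchanged, and unequal detection moves it in either direction.

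**The case against.** The strongest reply is that little depends on this list. It is labelled exploratory, the main comparison is an unadjusted log-rank test, and the secondary Cox model names no factors. All of that stands. The list is nevertheless the only place where prognostic factors for adjustment are named, so an analyst could well take the secondary model's covariates from it.

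A second reply is that the factors are said to be evaluated, and the next sentence turns to the effect of baseline quality of life on survival. The passage may therefore describe a prognostic study, not an arm comparison. That reading is possible. But the opening words say the analysis adjusts, and nothing separates the two purposes.

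A third reply concerns mechanism. Invasion and nodal spread are tumour features, not effects of the surgical approach. One surgeon operates in both arms, with the same node and abandonment text. This is right, and it rules out an inference that a reader might draw: that adjusting removes part of the treatment effect or pulls it towards no difference. Bias needs arm-dependent ascertainment, and its direction is open. The protocol does leave room for such a difference: the trial is open-label, nodes go to frozen section on the surgeon's suspicion, and access differs between arms.

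Finally, handling of missing covariates may sit in an analysis plan that is not shown, and the baseline cervical or cone biopsy may give some information on depth. Both are fair. The exclusion therefore follows only under a complete-case fit on specimen depth. The absence of a missing-data rule is not itself the point; the stated choice of covariates is.

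**Conclusion.** The point holds for the exploratory model, and for the secondary model if it takes up the same list. Two listed factors are established at the randomised operation and one is undefined. A complete-case fit on specimen depth would conflict with the promise to include all randomised patients.

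A reader might go further and conclude that the adjusted analysis is neither randomised nor intention-to-treat. The text does not support that. Patients can still be analysed in their allocated arms; intention-to-treat is lost only if patients are dropped, or if arm is replaced by treatment received. Nor is treatment type shown to be a consequence of surgical findings, since it may simply be the arm.

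The size cannot be derived from the documents. The 15 to 111 patients rest on assumed abandonment rates of 2% to 15%. The shifts of about 6% to 10% in the hazard ratio rest on the assumed prevalence, prognostic effect and a 100% against 70% detection gap; with equal detection there is essentially no shift. Any share of events lost would need a further assumed event risk, so none is claimed. The primary comparison is untouched. This is a modest point about a non-primary analysis, worth correcting because the correction is easy.

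**What to change.** In Phase II analysis, replace the covariate list as follows.

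- In any Cox model that estimates the arm effect, secondary or exploratory, include the randomised arm and adjust only for factors known before randomisation: age, clinical stage, tumour size on baseline imaging, histology and grade from biopsy, and ECOG status.
- Put depth of invasion, nodal status and any treatment received in a separate prognostic model, and state that it is not used for the arm comparison.
- State what treatment type means.

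These baseline factors, or the examinations that yield them, are already collected, so no new data are needed. The cost is wording in one section and slightly less prognostic precision in the adjusted model.
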